### Sample size

We are aiming for a sample size of 40 schools (20 per arm). Assuming a comparator mean of 7.08 min of energisers scheduled daily, a standard deviation of 4.88, an average of five classes per school and an intraclass correlation coefficient (ICC) of 0.11, based on our previous trial [13], a sample of 40 schools is sufficient to detect (with 80% power, an alpha of 0.05) a mean difference of approximately 2.38 min of daily energisers.

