**Methods:**

A cluster randomised controlled trial will be conducted in 50 primary schools within the Hunter New England, Illawarra Shoalhaven, Murrumbidgee and Northern New South Wales (NSW) Local Health Districts of NSW Australia. Schools will be randomly allocated to receive either usual support or the multi-strategy sustainability intervention that includes: centralised technical assistance from a trained project officer; formal commitment and mandated change obtained from school principals; training in-school champions; reminders for teachers; educational materials provided to teachers; capturing and sharing local knowledge; and engagement of parents, carers and the wider school community. The primary trial outcome will be measured via a teacher logbook to determine the between-group difference in the change in mean minutes of energisers scheduled across the school day at 12 and 24-month follow-up compared to baseline. Analyses will be performed using an intention to treat framework. Linear mixed models will be used to assess intervention effects on the primary outcome at both follow-up periods.

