### Participants and recruitment

*Schools:* Eligible schools will include all government, Catholic and independent (private) primary schools that have received *Physically Active Children in Education (PACE*) training to support their implementation of weekly physical activity, including energisers. Schools will be excluded if they are participating in another physical activity intervention or cater exclusively for children with special needs. Principals from eligible schools will be provided with a study information package and asked to provide online written informed consent.

*Teachers:* All classroom teachers from eligible and consenting schools will be randomised to receive the sustainability strategy and an invitation to participate in data collection. Strategies will be employed to ensure high recruitment rates are achieved, including delivering a series of two follow-up emails and a phone call reminder to schools [30]. To maximise principal and teacher survey participation rates, evidence-based strategies will be delivered, including sending two email reminders to teachers (one week apart) and one follow-up phone call reminder to In-school Champions (ISCs) to complete the survey, as well as distribution of a AUD$30 online gift card from a national grocery store for each principal and teacher who completes a survey in gratitude for their time. To maximise the retention of schools over the study period, strategies will be enacted including the delivery of non-program resources (including a pen, post-it notepad, and stickers for each class), to each teacher during data collection, as well as a letter of appreciation from the project team outlining the broad positive impact of their participation [31–33]. Previous studies conducted by the research team utilising such strategies have yielded school and or teacher participation rates of > 80% and attrition of < 20% [13, 34, 35].

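### The abstract gives 50 schools and the sample-size section 40, and the stated 80% power for 2.38 min fits only 40 schools analysed in full, so the article must say which number is randomised and which is analysed

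*Protocol article*

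**What the plan says.** The Methods paragraph of the abstract states: "A cluster randomised controlled trial will be conducted in 50 primary schools". The Sample size section states: "We are aiming for a sample size of 40 schools (20 per arm"). It then says that "a sample of 40 schools is sufficient to detect (with 80% power, an alpha of 0.05) a mean difference of approximately 2.38 min". Its inputs are "a standard deviation of 4.88", "an average of five classes per school" and "an intraclass correlation coefficient (ICC) of 0.11", taken from the team's previous trial. It also gives a comparator mean of 7.08 min, which the calculation of a difference does not use.

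The Statistical analysis section makes 24 months the primary endpoint. It plans a linear mixed model on all available data, assuming that data are missing at random. The Participants and recruitment section reports that the team's earlier studies had "school and or teacher participation rates of > 80% and attrition of < 20" per cent. The Sample size section does not mention attrition, and no section connects 40 with 50.

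**The concern.** Two current statements of the trial's basic design number differ by 10 schools. The difference matters because the power statement depends on which count is the number randomised and which is the number contributing data at 24 months. If 40 is the number randomised, any loss of schools or teachers over two years takes the trial below its stated power. If 50 is the number randomised, the 40-school calculation may be the position after attrition, but the article does not say so. A reader of the results paper would then be unable to tell whether 40 randomised schools met the target or fell 20% short of it.

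**Working it through.** **Inputs.** All are from the Sample size section unless noted: SD 4.88; m = 5 classes per school; ICC 0.11; 20 schools per arm; power 80%; alpha 0.05. Allocation is 1:1 (Randomisation and blinding). Sidedness is not stated; two-sided is assumed because it reproduces the plan's figure, whereas one-sided alpha with the normal approximation gives 2.06 min.

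**Formulae.** With k schools per arm:
- Design effect: DE = 1 + (m − 1) × ICC
- Standard error of the difference: SE = SD × √(2 × DE / (k × m))
- Detectable difference and power: noncentral t on 2k − 2 degrees of freedom, two-sided 0.05

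**Reproducing the plan's figure** (k = 20, m = 5):
- DE = 1 + 4 × 0.11 = 1.44
- SE = 4.88 × √(2 × 1.44 / 100) = 4.88 × √0.0288 = 0.828
- With 38 df, the detectable difference at 80% power is 2.381 min, and power at 2.38 min is 80.0%.
- The normal approximation gives 2.320 min, and 82.0% power at 2.38 min. The t version is therefore the one that matches.

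The stated 2.38 min uses all 40 × 5 = 200 classes, so it contains no loss.

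**Power at 2.38 min under each reading** (same formula, t-based, equal loss in both arms):

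| Randomised | Loss assumed by 24 months | Analysed | SE | Detectable difference (min) | Power at 2.38 min |
|---|---|---|---|---|---|
| 40 | none | 40 schools × 5 | 0.828 | 2.38 | 80.0% |
| 40 | 10% of schools | 36 × 5 | 4.88 × √(2.88/90) = 0.873 | 2.52 | 75.4% |
| 40 | 20% of schools | 32 × 5 | 4.88 × √(2.88/80) = 0.926 | 2.68 | 70.1% |
| 40 | 20% of teachers | 40 × 4 (DE 1.33) | 4.88 × √(2.66/80) = 0.890 | 2.56 | 74.1% |
| 50 | 20% of schools | 40 × 5 | 0.828 | 2.38 | 80.0% |
| 50 | 20% of teachers | 50 × 4 (DE 1.33) | 4.88 × √(2.66/100) = 0.796 | 2.28 | 83.4% |
| 50 | none | 50 × 5 | 4.88 × √(2.88/125) = 0.741 | 2.12 | 88.3% |

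**Link between the two numbers.** 40 / (1 − 0.20) = 50. The abstract's count is exactly what 40 analysed schools would require at the quoted attrition ceiling.

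**The case against.** The strongest reply is that nothing is wrong with the power. Since 50 × 0.8 = 40, the abstract may give the number recruited and the Sample size section the number retained, in which case 80% power for 2.38 min is right. This stands to the extent that the calculation has no arithmetic error and is easily checked. A reader might infer from the missing attrition allowance that the trial does not deliver 80% power. The article does not support that, because it would require 40 to be the number randomised, which no section states. Equally, no section says that 50 is the inflated target; that is an inference from the arithmetic.

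Four further points narrow the claim.

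- The quoted attrition is an upper bound from earlier studies, and its level (school or teacher) is not specified. The 70% figure is therefore the ceiling case, with all loss as whole schools.
- It is tempting to reduce the class count further by the roughly 88% logbook completion quoted under the primary outcome. That step is unsafe. The five classes per school come from one of the trials cited for that completion rate and may already count only responding classes. The rate may also overlap with the attrition figure.
- The planned model analyses change over three time points, while the sample-size formula is a simple two-group comparison. No within-teacher or within-school correlation over time is given, so the true power of the planned analysis cannot be derived here.
- Baseline collection was due to run to October 2023 and the article appeared on 7 October 2023. The risk that recruitment stops early at 40 is therefore probably largely past.

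A journal article may also leave an attrition allowance to the full protocol, so that omission alone would not be a finding. The conflict between 50 and 40 remains, because the article states both.

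**Conclusion.** The point holds as an internal inconsistency, not as an arithmetic error. The article gives two school counts and does not say which is randomised and which is analysed. Its power statement is correct for 40 schools with five classes each contributing at 24 months, and for nothing smaller.

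- If 50 are randomised and up to 20% are lost, the stated power is met.
- If 40 are randomised, power at 2.38 min is about 75% with 10% school loss. At the 20% ceiling it is about 70% for whole-school loss, with a detectable difference of about 2.7 min, or about 74% for teacher loss.

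These figures rest on the plan's own SD, ICC and cluster size, two-sided testing, equal loss across arms, no contribution at 24 months from lost schools or teachers, and no gain or loss of precision from the baseline measurement. The text needs correcting because the trial relies on this sample-size and power statement.

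**What to change.** Give one number of schools to randomise in both the abstract and the Sample size section, and say whether 40 is the number randomised or the number expected in the 24-month analysis.

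- **If 50 is right:** *Randomise 50 schools (25 per arm); allowing for up to 20% attrition, 40 schools with five classes each at 24 months give 80% power for 2.38 min.*
- **If 40 is right:** correct the abstract to 40, and restate the power as about 70% for 2.38 min, or the detectable difference as about 2.7 min, at 20% school loss.

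The cost is a wording change in two places; no further schools are needed. Under the second option the published power statement becomes less favourable.

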### Research trial governance

This study has employed a research co-production approach in its design [55]. An external multi-disciplinary Advisory Group, consisting of 16 members including education policy makers, health promotion practitioners, Aboriginal Health Officers, as well as researchers with expertise in physical activity, implementation science, behavioural science, education and public health will oversee all aspects of the planning, implementation and evaluation of the project. A project team consisting of research staff and practitioners will conduct the study according to study protocol. The Advisory Group will oversee the project dissemination plan including all publications and reports to stakeholders. Authorship will conform to the International Committee of Medical Journal Editors guidelines.

### Trial discontinuation or modification

Our Advisory Group will convene once a quarter to ensure the study is abiding by the prescribed ethics and timeline. It is not anticipated that any events would occur that warrant discontinuing the trial. However, any unforeseen adverse events will be recorded and assessed by the trial Advisory Group and reported to the HNE Human Research Ethics Committee (primary approval committee), with advice sought regarding required action. The trial registration record will be updated with any protocol modifications, and any deviations from original protocol will be reported in study outcome papers.

## Discussion

Physical inactivity is a leading cause of death and disability in Australia and internationally [56, 57] and is identified as a priority health issue [1, 2]. Improving children’s activity levels is key to reducing the development of both short and long-term health burdens [58, 59]. School-based physical activity policies effectively improve child physical activity levels [50, 60, 61]. However, sustaining their implementation remains a considerable challenge globally [18, 19]. In Australia alone, approaches to sustain the implementation of school-based policies that mandate minimum periods for structured physical activity have the potential to improve the health, well-being and chronic disease risk of two million students [62]. This study is one of the first RCTs to test the effectiveness and efficiency of theoretically and empirically informed strategies to improve the sustainability of an EBI targeting a chronic disease risk factor in schools. The proposed trial will be seminal for the field, translate into fundamental outcomes in the knowledge base of sustainability research, and provide a platform for future research examining the sustainability of effective EBIs in the school setting.

## Data Availability

All study materials are available from the research team upon request to lead investigators.

## Abbreviations

AACTT: Action, Actor, Context, Target, Time
APEASE: Affordability, Practicality, Effectiveness and cost effectiveness, Acceptability, Side-effects/safety and Equity
BCW: Behaviour Change Wheel
CONSORT: Consolidated Standards of Reporting Trials
DoE: Department of Education
ERIC: Expert Recommendations for Implementing Change
EBI: Evidence-based intervention
HNE: Hunter New England
ICC: Intraclass correlation coefficient
ISC: In-school champion
MVPA: Moderate-to-vigorous physical activity
NHMRC: National Health and Medical Research Council
NSW: New South Wales
PACE: Physically Active Children in Education
PE: Physical Education
RCT: Randomised controlled trial
REDCap: Research Electronic Data Capture
StaRI: Standards for Reporting Implementation Studies
TDF: Theoretical Domains Framework
